### Study design and overview

Study participation will last 6 weeks and include 3 virtual visits (10–40 minutes each; baseline, quit date, and end of the study) and 5 daily EMAs for 42 days. After the baseline visit, participants will complete daily EMAs for 2 weeks in the pre-quit period and for 4 weeks in the post-quit period (see Fig 1). Participants will be required to complete EMAs 30 minutes after their preset waking time (morning diary), 3 random times (random sampling) during each day and one hour before bedtime (evening diary), to assess any smoking-related triggers and behaviors and smoking events and to complete biochemical verification of smoking status via iCO Breathlyzer in the evening [40] Participants can also initiate prompts when they smoke. In addition, participants will wear an ActiWatch (Motion Watch 8; CamNTech, Ltd) [41] during the 6-week study period (See Measures section for details). Participants will complete a follow-up assessment 4 weeks after their end of study to assess relevant variables including smoking status.

**Fig 1 pone.0334129.g001:**

Study overview.

### Study setting and population

Participants (N = 80) will be adults who smoke cigarettes and attend one of 11 Quitcenters across the state of New Jersey between June 2026 and June 2028. Individuals seeking smoking cessation services at the Quitcenters will be given a verbal description of the study during their first visit, and interested individuals will be screened for study eligibility. Eligibility criteria are: 1) household income <200% of the federal poverty line, [42] 2) a score ≥ 4 on the Rapid Estimate of Adult Literacy in Medicine-Short Form (REALM-SF), [43] 3) willingness to quit smoking 14 days after the baseline visit, 4) ≥ 18 years of age, 5) an expired CO level ≥ 7 ppm, 6) currently smoking ≥ 5 cigarettes per day, 7) no overnight shiftwork, 8) not currently using potentially sedating medications, and 9) no contraindications to using NRT (per self-report). All participants will provide written informed consent prior to participation in the study.

### Procedure

Participants will be provided an Actiwatch, and an iCO Breathalyzer. Participants who do not have a smartphone that meets the minimum criteria to support the Insight^TM^ app [44] will also be provided a phone. Participants will be instructed regarding using the Insight^TM^ smartphone application, Actiwatch, Breathalyzer, and EMA procedures. Participants will complete questionnaires at the baseline visit, including the pre-treatment assessment of sleep, other tobacco use, past/current medical history, provide a CO breath sample to verify smoking status, and measure of neck circumference.

Participants will use the Insight^TM^ app [44] to record subjective sleep and wake times and will wear an Actiwatch to obtain objective sleep data continuously for the entire 6-week study period. At the end of the study, participants will return the Actiwatch and study phone (if they did not use their own smartphone) via mail or curbside drop-off. All participants will download the Insight^TM^ mHealth application [44], which includes a “Call Staff” function/button that automatically calls study staff (e.g., if the participant has problems completing EMAs). The Insight^TM^ app [44] also includes a “Payment” button which, when pressed, indicates the number of EMAs that have been prompted and completed and the current level of compensation based upon the up-to-the-moment percentage of EMAs completed. All participants will wear Actiwatch, complete 3 virtual visits, and complete 5 daily EMAs (i.e., 3 random,1 morning and 1 evening diaries; see Measures section for details). Participants will receive $15 for completing each visit ($45 in total) and will be compensated based upon the percentage of Daily and Random EMAs completed (i.e., $70 for completing 50%−74% of prompted EMAs, $90 for completing 75%−89% of prompted EMAs, and $120 for completing 90% or more prompted EMAs). An additional $50 payment will be awarded to participants for wearing the Actiwatch at least 90% of the time. This payment will be provided after participants return the Actiwatch. There will be additional $10 payment for those who complete the one-month follow-up survey. The use of personal vs. study-provided phones will be examined as a covariate in all analyses. Data collection is expected to be completed by August 2028.

This study was approved by the Rutgers Institutional Review Board (Pro2022002184). All participants will provide written informed consent prior to participation in the study. The consent process includes a full explanation of the study’s aims, procedures, potential risks, and benefits. Participants will be informed of their right to withdraw from the study at any time without any consequence. Confidentiality and anonymity of participants will be maintained throughout the study.

### Measures

**Virtual visits (i.e., baseline, quit date, and end of study):** baseline visit assessments will assess demographic, anthropometric (e.g., self-reported height and weight), sleep-related characteristics (e.g., STOP-BANG [45]), tobacco use characteristics (e.g., use of e-cigarettes), and other mental diagnoses, medical history, tobacco/e-cigarette and other substance use, and multiple constructs related to smoking lapse (e.g., stress, affect, anxiety). Quit date visit assessments will include participant’s readiness to quit, biochemical verification of smoking abstinence, and multiple constructs related to smoking lapse (e.g., stress, affect, anxiety). End of study visit assessments will assess participants’ experience of using the app, biochemical verification of smoking abstinence, and multiple constructs related to smoking lapse (e.g., stress, affect, anxiety).

**EMAs:** Three types of EMA sampling will be used: daily diaries, random sampling, and event sampling. Daily diary assessments will be completed

twice every day (30 minutes after waking and 1 hour before bedtime), and questions will refer to the previous few hours and the current moment (Table 1). The phone audibly and visually cues each EMA. If the participant does not respond after three prompts, the assessment will be recorded as missed. Participants will self-initiate event sampling EMAs. Participants will be instructed to complete “smoking assessments” when they smoke before the quit date and “lapse assessments” if they smoke after the quit date. EMA items will assess smoking (e.g., cigarettes smoked, time since last cigarette), use of NRT, mood (e.g., sadness, happiness), motivation to quit smoking, availability of cigarettes, and social setting. Daily smoking abstinence will be calculated using a standard algorithm from multiple assessments of smoking throughout the EMAs. The Actiwatch [46] will collect data on activity (i.e., arm motion) and ambient light that is related to sleep. Actigraphy data will be downloaded from the actigraphy watch into the Motionware software (version 1.4.25) for analysis, management, and exportation. Total sleep time, sleep start and end times, sleep onset latency, sleep duration, and sleep efficiency will be calculated objectively with a standard algorithm [41]. Mid-sleep time will be calculated as the midpoint between sleep start and end times as an indicator of the circadian phase [41].

**Table 1 pone.0334129.t001:** EMA Items of the study.

EMA	MEASURE
Morning Daily Diary	Cigarettes smoked
	Social interactions and support
	NRT use
	Side Effect Items
	Alcohol Consumption
	Sleep Items
End of Day Daily Diary	Cigarettes smoked
	Other substance use
	iCO Breath test
Random/Event EMAs	Recency of smoking
	Urge to smoke
	Stress
	Availability of cigarettes
	Recent alcohol use
	Cessation motivation
	Interaction with smokers
	Social setting/location
	Reasons for lapse
	Cigarette reward value
	Lapse warning signs

### Power

A two-step power analysis was conducted. In step 1, G*Power 3.1.9.2.[47] was used to estimate power for a traditional regression model. Based on our preliminary study, [48] an effect size of *f*^*2*^ = .08 was used for the current study. Using G*Power, it was estimated that a sample of 177 would be needed to observe the effect size (*f*^*2*^ = .08) of sleep duration/quality and smoking abstinence to achieve power of.80 with an alpha level of.05 for six predictors. However, G*Power cannot estimate the sample size for multilevel models (e.g., nested data). Therefore, in step 2, we examined the number of unique observations needed to estimate the accurate sample size for multilevel models given the multilevel structure of the data.[49] West, Ryu, Kwok, and Cham’s (2011) equation used for step 2 is below:

$$N_{effective}=\frac{nL_{1}nL_{2}}{[1+(nL_{1}–1)𝐈𝐂𝐂]}$$

This equation accounts for level 1 (daily diary; nL1) and level 2 (participant; nL2) sample sizes, and the intraclass correlation (ICC) which is the proportion of the variance in the dependent variable that is attributed to variability between people. Based on prior research, a moderate amount of within-person variation is expected for smoking cessation (range ICC = 0.2–0.4). Using this information of the sample size of 42 (7X6) days (Level 1; nL1) and a conservative ICC value of 0.2 from our previous work on sleep and smoking cessation [48] it was estimated that approximately 39 participants (Level 2; nL2) will provide sufficient power. With these estimates the *N*_*effective*_ is 179 independent observations which exceeds the required 177 independent observations from step 1. The sample size of 50 participants or more will provide sufficient power for the proposed study, 50*(42 days) observations; n = 2100 (n = 1680, taking into consideration expected EMA compliance rates of 80%). Trained staff will closely monitor participant compliance rates.

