### Analytic approach

Descriptive statistics will summarize the distributions of outcomes and demographic characteristics. We will also explore any differences in outcomes by demographic characteristics (e.g., sex, race). If more than 10% of the outcomes are missing, methods for missing data will be considered. To identify bidirectional and temporal associations of daily abstinence and sleep dysregulation via EMA and wrist worn sensors during the first four weeks of a smoking cessation attempt (N = 80), cross-lagged models (see Fig 2) will be tested to examine 1 simultaneously) the association of sleep dysregulation with subsequent changes in daily abstinence, and 2) the association of daily abstinence with subsequent changes sleep dysregulation using Actiwatch. We will use multilevel models with lagged effects in SAS 9.4 software (SAS Institute, Cary, North Carolina) to test the temporal associations between daily sleep dysregulation and smoking abstinence. Two-level models will be conducted with 80 participants who complete the assessments over the 4 weeks of post-quit. The total number of EMAs are estimated to be 1792 ~ 2240 (80% to 100% compliance) clustered within 80 participants. The models will use an AR [1] error covariance structure to account for correlations between consecutive sleep and abstinence observations.[50] When *the outcome variable is smoking abstinence*, either sleep duration, bedtime, sleep latency, or sleep efficiency will be the predictor variable. When *the outcome variable is a nighttime sleep measure* (e.g., duration, sleep maintenance efficiency, sleep onset, sleep offset), daily smoking abstinence will be the predictor variable (alternatively, other cessation outcomes (e.g., urge) will be also tested). Variances for sleep dysregulation and abstinence measures will be decomposed to within-person and between-person components. Within-person variables will be centered at the person mean, so that positive values indicate scores higher than the person’s cross-day average. Between-person variables will be centered at the sample mean so that positive values indicate higher scores than others in the sample. A stepwise procedure will be used for variable selection, and variables from the procedure (e.g., sex, ethnicity, age, other tobacco/e-cigarette use, mental diagnosis, NRT use, BMI) will be included as covariates in all models. In addition, sensitivity analysis will be conducted to evaluate the robustness of the results from the analyses. We attend to sex as a biological variable by: 1) recruiting both sexes, 2) stratifying randomization by sex, and 3) exploring any differences in outcomes by sex.

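### The power calculation counts 42 days per person, but the models described use the 28 post-quit days in 80 participants, so no stated power figure describes the dataset to be analysed

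*Protocol article*

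**What the plan says.** **Power.** Step 1 is a conventional regression calculation with f² = 0.08, set up "to achieve power of.80 with an alpha level of.05 for six predictors", which returns 177 observations. Step 2 converts clustered days into an effective number of independent observations. Its inputs are "a conservative ICC value of 0.2 from our previous work on sleep and smoking cessation" and 42 days per person ("Using this information of the sample size of 42 (7X6) days (Level 1; nL1"). The ICC range expected from prior research is given as 0.2 to 0.4. The result for 39 participants "is 179 independent observations which exceeds the required 177 independent observations from step 1". The section then states that 50 or more participants are enough and counts 50 × 42 = 2100 observations, or 1680 at 80% EMA compliance.

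**Study aim, and Study design and overview.** The aim concerns the first four weeks of the quit attempt. The 42 days consist of two pre-quit weeks and four post-quit weeks.

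**Analytic approach.** "Two-level models will be conducted with 80 participants who complete the assessments over the 4 weeks of post-quit". The expected data volume is given as follows: "The total number of EMAs are estimated to be 1792 ~ 2240 (80% to 100% compliance) clustered within 80 participants".

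**Study setting and population.** Planned enrolment is 80.

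**The concern.** A power calculation should describe the data that the models will use. Here the two adjacent sections differ in both dimensions: 42 days against 28, and 39 or 50 participants against 80. The 14 pre-quit days enter the power calculation but no model that the article describes. The stated margin in step 2 is only two observations (179 against 177), so removing a third of the days could overturn the claim.

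The enrolled number is also never derived. The only thresholds in print are 39 and 50. If recruitment were slow, the Power section could be cited to stop at 50, so it matters whether 50 holds up on the days analysed and over the article's own ICC range.

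**Working it through.** **Inputs, all from the article.** f² = 0.08, alpha 0.05, target power 0.80, six predictors; ICC 0.2 used, range 0.2 to 0.4; 42 days in the Power section; 28 post-quit days and 80 participants in the Analytic approach; 80% EMA compliance.

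**Step 1 reproduced.** The overall F test of six predictors has noncentrality 0.08 × N and N − 7 denominator degrees of freedom. The smallest N with power of at least 0.80 is 177 (power 0.801), as stated.

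**Step 2 reproduced.** With d days, n participants and intraclass correlation ICC, the article's equation is N_effective = d × n / [1 + (d − 1) × ICC].

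- 42 days, 39 participants, ICC 0.2: 1638 / 9.2 = 178.0. The article states 179. The difference is trivial and the value still exceeds 177.

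**Which days are in the models.** 80 × 28 = 2240, and 0.8 × 2240 = 1792. These are exactly the two counts in the Analytic approach, so that section is built on 28 days per person. The Power section's 2100 and 1680 are 50 × 42 and 0.8 × 2100.

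**Step 2 with the 28 days analysed.** The denominator is 1 + 27 × 0.2 = 6.4 at ICC 0.2 and 1 + 27 × 0.4 = 11.8 at ICC 0.4. Power comes from the step 1 test with N_effective in place of N.

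| Participants | ICC 0.2: N_effective (power) | ICC 0.4: N_effective (power) |
|---|---|---|
| 39 | 1092 / 6.4 = 170.6 (0.78) | 1092 / 11.8 = 92.5 (0.46) |
| 50 | 1400 / 6.4 = 218.8 (0.89) | 1400 / 11.8 = 118.6 (0.59) |
| 80 | 2240 / 6.4 = 350.0 (0.99) | 2240 / 11.8 = 189.8 (0.83) |

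Participants needed to reach 177:

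- ICC 0.2: 177 × 6.4 / 28 = 40.5, so 41.
- ICC 0.4: 177 × 11.8 / 28 = 74.6, so 75.

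**With compliance inside the equation.** This assumes that 80% EMA compliance means 0.8 × 28 = 22.4 usable days. The denominators become 5.28 (ICC 0.2) and 9.56 (ICC 0.4).

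- 39 participants, ICC 0.2: 873.6 / 5.28 = 165.5 (power 0.77). Needed: 177 × 5.28 / 22.4 = 41.7, so 42.
- 80 participants: 1792 / 5.28 = 339.4 (power 0.99) at ICC 0.2, and 1792 / 9.56 = 187.4 (power 0.83) at ICC 0.4. Needed at ICC 0.4: 177 × 9.56 / 22.4 = 75.5, so 76.

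**Which input matters most.** At ICC 0.2, going from 42 to 28 days raises the requirement from 39 to 41. At 28 days, going from ICC 0.2 to 0.4 raises it from 41 to 75. The article calls 0.2 conservative, but in this equation a lower ICC gives a larger effective sample, so 0.2 is the favourable end of its range.

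**The case against.** The strongest reply is that the operative conclusion survives. Nobody plans to enrol 39. The Power section ends at 50 or more, a minimum that includes 80. At ICC 0.2, 50 participants over 28 days still clear 177 comfortably, and enrolling above a stated minimum is ordinary practice. This stands: the participant numbers do not contradict each other; 80 is simply not derived. It does not rescue the minimum of 50 at the upper end of the stated ICC range, nor the specific claim about 39.

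A second reply is that the 28-day models are not the only analyses. The article also mentions descriptive, alternative-outcome and sensitivity analyses, and the Abstract and Discussion speak of both pre-quit and post-quit periods. That limits the point to the inferential models described; none of them is described as using pre-quit days.

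A third reply is that 80% EMA compliance need not mean 22.4 usable days. Daily abstinence is built from several assessments, so one missed prompt need not lose a day, and objective sleep comes from the Actiwatch. This also stands. The 22.4-day results are a sensitivity check, and the 28-day results do not depend on them.

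A reader might go further and infer that the study is underpowered, or that dropout or lost consecutive-day pairs would make it so. The documents do not support this. Eighty participants exceed 80% power over the whole stated ICC range. The article gives no dropout rate, and the figure with the lag structure is not available, so any count of lost pairs would rest on outside assumptions. Labelling the 1792 to 2240 person-days as EMAs is a wording slip.

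**Conclusion.** The point holds as an error in the justification, not in the sample size. The stated claim that 39 participants exceed the requirement is false for the 28 days to be analysed, although the shortfall is small (170.6 against 177). The statement that 50 suffice holds only towards the favourable end of the article's ICC range. The planned 80 are adequate on the article's own method.

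This takes as given the article's effect size, its overall six-predictor test, its effective-sample equation and its ICC range. Whether that method suits lagged models of daily abstinence was not examined here.

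**What to change.** Rewrite the step 2 paragraph in the Power section:

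- Set the level-1 size to 28 post-quit days and the level-2 size to 80 participants. Show 22.4 days as a labelled assumption about compliance.
- Give results over ICC 0.2 to 0.4: N_effective of about 187 to 350, with power of about 0.83 to 0.99.
- Replace the 39-participant, 50-participant and 2100/1680 figures with these, so that the paragraph supports the enrolled 80 and agrees with the Analytic approach.
- Stop describing ICC 0.2 as conservative, since it is the low end of the stated range.

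The cost is one paragraph. Enrolment, data collection and the planned models do not change.

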### Analytic approach

Descriptive statistics will summarize the distributions of outcomes and demographic characteristics. We will also explore any differences in outcomes by demographic characteristics (e.g., sex, race). If more than 10% of the outcomes are missing, methods for missing data will be considered. To identify bidirectional and temporal associations of daily abstinence and sleep dysregulation via EMA and wrist worn sensors during the first four weeks of a smoking cessation attempt (N = 80), cross-lagged models (see Fig 2) will be tested to examine 1 simultaneously) the association of sleep dysregulation with subsequent changes in daily abstinence, and 2) the association of daily abstinence with subsequent changes sleep dysregulation using Actiwatch. We will use multilevel models with lagged effects in SAS 9.4 software (SAS Institute, Cary, North Carolina) to test the temporal associations between daily sleep dysregulation and smoking abstinence. Two-level models will be conducted with 80 participants who complete the assessments over the 4 weeks of post-quit. The total number of EMAs are estimated to be 1792 ~ 2240 (80% to 100% compliance) clustered within 80 participants. The models will use an AR [1] error covariance structure to account for correlations between consecutive sleep and abstinence observations.[50] When *the outcome variable is smoking abstinence*, either sleep duration, bedtime, sleep latency, or sleep efficiency will be the predictor variable. When *the outcome variable is a nighttime sleep measure* (e.g., duration, sleep maintenance efficiency, sleep onset, sleep offset), daily smoking abstinence will be the predictor variable (alternatively, other cessation outcomes (e.g., urge) will be also tested). Variances for sleep dysregulation and abstinence measures will be decomposed to within-person and between-person components. Within-person variables will be centered at the person mean, so that positive values indicate scores higher than the person’s cross-day average. Between-person variables will be centered at the sample mean so that positive values indicate higher scores than others in the sample. A stepwise procedure will be used for variable selection, and variables from the procedure (e.g., sex, ethnicity, age, other tobacco/e-cigarette use, mental diagnosis, NRT use, BMI) will be included as covariates in all models. In addition, sensitivity analysis will be conducted to evaluate the robustness of the results from the analyses. We attend to sex as a biological variable by: 1) recruiting both sexes, 2) stratifying randomization by sex, and 3) exploring any differences in outcomes by sex.

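### The modelled sample is described as 80 completers although exactly 80 are recruited, so the stated 1,792–2,240 observations allow for missed prompts but not for dropout, and they are person-days, not EMAs

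*Protocol article*

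**What the plan says.** Study setting and population fixes the recruited number: "Participants (N = 80) will be adults who smoke cigarettes and attend one of 11 Quitcenters". Study design and overview schedules daily assessment "for 2 weeks in the pre-quit period and for 4 weeks in the post-quit period".

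Analytic approach then describes the modelled sample: "Two-level models will be conducted with 80 participants who complete the assessments over the 4 weeks of post-quit". The next sentence gives its size: "The total number of EMAs are estimated to be 1792 ~ 2240 (80% to 100% compliance) clustered within 80 participants".

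The article states no dropout rate, no replacement of withdrawals and no enrolment above 80. Procedure says that "Participants will be informed of their right to withdraw from the study at any time without any consequence". On incomplete data, Analytic approach says "If more than 10% of the outcomes are missing, methods for missing data will be considered" and promises a sensitivity analysis without describing it.

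**The concern.** The recruited number and the number completing four post-quit weeks are both 80. They can be equal only if nobody leaves a six-week study with five prompts a day, a burden that the Discussion itself lists as a limitation. The one reduction in the count is for compliance, and it is applied to all 80 people.

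What is at stake is mainly who enters the models. As soon as one person drops out, the sentence can be followed in two ways: keep everyone for as long as they provide data, or keep only those who finished. The second selects on something that happens after the quit date. Hypothesis 1 includes an effect that fades over time, and the models separate between-person from within-person variation. If people who relapse or sleep badly are more likely to leave, a completers-only set could distort the time trend and the between-person estimates.

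A smaller matter is the label. A reader who takes the range as a number of EMAs will misjudge both the data volume and the unit of analysis.

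**Working it through.** **Inputs from the article.** 80 recruited (Study setting and population); 4 weeks = 28 post-quit days and 5 EMAs a day (Study design and overview); compliance 80% to 100% (Analytic approach); 177 effective observations required, ICC range 0.2–0.4 with 0.2 used, and the effective-sample formula (Power). Dropout rates are not given, so those below are assumptions.

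**1. Reproduce the stated count.**
- 80 × 28 × 1.00 = 2,240
- 80 × 28 × 0.80 = 1,792

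Both ends match exactly. All 80 people are counted for the whole 28 days, so participant-level dropout is set to zero.

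**2. Check the unit.** At five EMAs a day, 2,240 × 5 = 11,200 and 1,792 × 5 = 8,960. The stated figures are person-days.

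**3. Count under assumed dropout, if dropouts contribute no post-quit days.**

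| Dropout | People | Person-days, 80% to 100% compliance |
|---|---|---|
| 10% | 72 | 1,613 – 2,016 |
| 20% | 64 | 1,434 – 1,792 |
| 30% | 56 | 1,254 – 1,568 |

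At 20% dropout the best case equals the article's own lower bound.

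**4. Effective sample size by the plan's formula.** N_effective = nL1 × nL2 / [1 + (nL1 − 1) × ICC]. As a check, the Power section's own case gives 42 × 39 / (1 + 41 × 0.2) = 1,638 / 9.2 = 178.0, against a stated 179; the difference does not matter here.

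With the 28 days actually modelled, each full participant contributes:
- ICC 0.2: 28 / (1 + 27 × 0.2) = 28 / 6.4 = 4.375
- ICC 0.4: 28 / (1 + 27 × 0.4) = 28 / 11.8 = 2.373

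N_effective if dropouts contribute nothing:

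| Dropout | ICC 0.2 | ICC 0.4 |
|---|---|---|
| 0% | 350 | 190 |
| 10% | 315 | 171 |
| 20% | 280 | 152 |
| 30% | 245 | 133 |

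Tolerable dropout before falling below 177:
- ICC 0.2: 177 / 4.375 = 40.5 people; 1 − 40.5/80 ≈ 49%
- ICC 0.4: 177 / 2.373 = 74.6 people; 1 − 74.6/80 ≈ 7%

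**5. Let dropouts contribute until they leave.** Assume ICC 0.4 and departure after 7 post-quit days. Each dropout then contributes 7 / (1 + 6 × 0.4) = 7 / 3.4 = 2.059. Summing over people:
- 10%: 72 × 2.373 + 8 × 2.059 ≈ 187
- 20%: 64 × 2.373 + 16 × 2.059 ≈ 185
- 30%: 56 × 2.373 + 24 × 2.059 ≈ 182

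All exceed 177. A shortfall needs heavy and very early loss: with 30% leaving after day 3, a dropout contributes 3 / (1 + 2 × 0.4) = 1.667, and the sum is 56 × 2.373 + 24 × 1.667 ≈ 173.

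**The case against.** The strongest reply is that the phrase about completing is loose wording and not an analysis rule. The following sentence accepts 80% compliance and keeps all 80 clusters, and no exclusion rule or completion threshold appears anywhere. If all 80 are analysed, nobody is selected out. This largely stands: the article does not prescribe a completers-only analysis. It does not remove the point, because the sentence cannot be applied as written once someone leaves, and nothing else in the article says who then enters the models. Leaving the finer detail of the analysis set to another document is normal, but here the article itself states a population and a count.

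Three stronger readings are tempting.

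- *The study would be underpowered with modest dropout.* The fall to 171, 152 or 133 needs both an ICC of 0.4 and dropouts who give no post-quit days. At the plan's ICC of 0.2 there is wide room. Power also puts the need at about 39 people and calls 50 or more sufficient, so 80 leaves 30 people (37.5%) above that figure.
- *Early lapsers, the subject of Hypothesis 2, would be lost.* Nothing in the article links lapse to dropout. Under Measures, participants who smoke after the quit date complete lapse assessments, and under Procedure payment depends on visits, EMA completion and watch wear, not abstinence. Hypothesis 2 is also worded at the level of days. The possible bias bears more on between-person estimates and on the attenuation in Hypothesis 1.
- *The 80% lower bound is a dropout allowance.* It could absorb a 20% loss of person-days from any cause, but it is labelled compliance and is spread over all 80 people.

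The missing-data sentence and the sensitivity analysis help only in part, since neither defines the modelled sample. The mislabelled unit is editorial: Power defines level 1 as the daily diary, so the intended unit can be recovered.

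**Conclusion.** The point holds as a matter of definition and reporting. The count of 1,792–2,240 is exact for 80 people over 28 days with no dropout, so it is a best case for retention, and its unit is person-days. Describing the same 80 as completers leaves open a restriction that could bias the between-person and time-trend estimates. That bias is conditional: it requires dropout to occur, the wording to be followed literally, and dropout to be related to relapse or sleep. The article gives no data on the first or the last, and the second may not be intended.

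The consequence for power is secondary. About 49% dropout is tolerable at ICC 0.2. N_effective falls below 177 at modest dropout only if the ICC is near 0.4 and those who leave contribute few or no days.

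**What to change.** Replace the completer wording in Analytic approach with, for example: *The two-level models will include all enrolled participants with at least one usable post-quit night-day pair, each contributing until dropout; completion of the four weeks is not required.*

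Restate 1,792–2,240 as person-days, and either say that the range assumes no dropout or give it under an explicit assumed rate, such as 1,434–1,792 at 20% if dropouts contribute no days.

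Do not raise N; the figures above give no reason to.

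The cost is two sentences and a slightly less favourable stated count. The models need no change, because mixed models already accept unequal numbers of days per person. Using all available data does not by itself remove bias if leaving depends on values never observed, so the planned sensitivity analysis would be a natural place to examine that. Recruitment is planned from June 2026, so the set can be fixed before any data are seen.
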